**SUMMARY**

**Rationale:** The ‘VIP (Vitality in Practice) in Insurance’ project is situated at a financial service provider in the Netherlands. This employer has great ambitions regarding the health of its employees and has already taken steps towards offering options to improve employees’ wellbeing. The management of the financial service provider identified low physical activity and relaxation levels, and high need for recovery, in its employees. Within the ‘VIP in Insurance’ program, an intervention was developed, in close cooperation with several representatives from the financial service provider, to decrease the need for recovery, by improving daily physical activity and relaxation behaviour at work.

**Objective:** The aim of this study is to evaluate an intervention program consisting of group motivational interviewing (GMI), supported by a social media platform, and/or environmental modifications, to decrease the need for recovery in office employees by increasing daily physical activity and relaxation levels.

**Study population:** The research population will consist of office employees of a financial service provider in the Netherlands.

**Study design:** In this study, a randomized controlled trial design will be employed, with pre-stratification on environmental modifications. At several floors of one of the main buildings of the financial service provider, two strata will be created with (6 wings) and without (7 wings) environmental modifications. Within each stratum, wings will be randomly assigned to GMI or no GMI. Randomisation will take place at wing level. The VIP project will consist of four research arms, i.e. (1) both GMI and environmental modifications, (2) environmental modifications/no GMI, (3) GMI/no environmental modifications, (4) no GMI/no environmental modifications (control group). Questionnaire data will be gathered at baseline (T0), at 6 months (T1), and at 12 months (T2) follow-up, in both employees and their teamleaders. In addition, cost-effectiveness and cost-utility analyses will be conducted from a societal and company perspective, and a process evaluation will be performed.

**Interventions**: (A). GMI intervention: teamleaders of the financial service will be trained to become a GMI-coach. After the two-day training, they will lead a GMI-group, consisting of their own employees. GMI will be applied for 3 sessions of 90 minutes each, over a period of 6 weeks, and will end with a follow-up meeting of 90 minutes, 2 months after the final session. The GMI groups will be supported by a social media platform. Employees will be stimulated through this platform to join physical and relaxation activity groups. (B). Environmental modifications: changes in the physical environment will be made to facilitate daily physical activity and relaxation at work, such as redesigning the coffee corners and the meeting rooms. The control group will receive no specific interventions and will proceed working as usual. A special VIP page will be created on the intranet for all employees, summing up the current offers of the financial service provider which are related to stimulating daily physical activity and relaxation. Furthermore, every two months, all employees will receive a newsletter about the VIP project.

**Main study parameters/endpoints:** Primary outcome measure of the study is need for recovery. Secondary outcome measures are daily physical activity, sedentary behaviour and relaxation/detachment. Furthermore, general health and work-related factors, such as exhaustion, sleep quality, stress, productivity and absenteeism will be measured. In addition, a subsample of 100 employees will be asked to wear an accelerometer for one week during the three measurement periods to measure sedentary and daily physical activity behaviour objectively.

**Hypothesis/anticipated results:** We hypothesize that the VIP program will significantly lower the need for recovery in office employees by increasing daily physical activity and relaxation, compared to the control group, both at short-term (6 months) and long-term (12 months) follow-up.

# 1. Introduction

In the past decades, the pressure of work has substantially increased. More than sixty percent of the employees in the EU experience that they are ‘working to tight deadlines’ (1). Working under pressure or working with high job demands has a strong negative impact on employees’ health and well-being, especially where employees have little decision latitude or little support from colleagues and/or managers. Employees with these unfavourable job characteristics are at risk to experience health problems, such as cardiovascular diseases (2), low back and neck pain (3) and psychological distress (4). Multiple work-related health problems seem to be preceded by a higher need for recovery (2;5). Need for recovery from work can therefore be considered as an important indicator for employees who are at risk for work related health problems (2;5).

The concept of need for recovery was deduced from the effort-recuperation model (6). It refers to the extent that the work task induces a need to recuperate from work induced effort. Need for recovery is characterised by temporary feelings of overload, irritability, social withdrawal, lack of energy and reduced performance (7). When time is lacking for recovery, initial load reactions are likely to accumulate, resulting in increased blood pressure (8), sleeping problems, (9) fatigue (10;11) and cardiovascular diseases (2).

For organisations, it seems worthwhile to invest in intervention programs that prevent higher need for recovery among their employees. Employees should pursue activities during work to recover. Detachment from work can be helpful for recovery. Psychological detachment is defined as the employee’s feeling to be mentally and/or physically away from work-related activities (12). Detachment has been identified to be particularly difficult when one has to deal with high job demands (7;13;14).

Earlier studies showed that breaks during work are needed to restore personal resources for future job demands (15). A break during work can be, for example, taking a walk or having coffee with colleagues. Engaging in breaks has been associated with positive affect and lower levels of negative feelings (15;16). Engaging in work-related tasks during breaks, and the resource depletion that goes along with it, should be avoided (17). Psychological detachment created during breaks is related to and reduces the need for recovery (12;14). When having insufficient time to detach from work, both emotional exhaustion (18;19) and the need for recovery (18) will increase. Following this line of reasoning, it is vital for organizations that employees regularly detach from work during the day.

It is hypothesized that physical activity and relaxation are useful strategies to improve detachment from work and lower the need for recovery from work. Previous studies showed that physical activity and relaxation were effective in altering physiological symptoms, somatic symptoms and psychological variables of stress (20). Physical activity programs are demonstrated to reduce work stress (21), absenteeism (22;23) and to improve job satisfaction (24). Relaxation helps to reduce blood pressure (25), heart rate and other symptoms of tension (26). It was shown that relaxation improves a positive mood (27), reduces anxiety, improves self-esteem and personal relationships (28). It can be concluded that both physical activity and relaxation can be useful in organizations for reducing employees' need for recovery from work.

# 1.2. Development of the VIP program

The VIP program was developed, using elements of the Intervention Mapping protocol (29). In this stepwise approach, a blueprint for the intervention was developed in close cooperation with the target group, combining scientific evidence with practice-based information. The management of the financial service provider indicated that improving daily physical activity and relaxation should be the main starting points for intervention development. Using interviews and questionnaires, we collected information on the employee’s attitude towards daily physical activity and relaxation. During these interviews, employees expressed that they generally have low daily physical activity and relaxation levels. Also, it was shown that they have a high need for recovery. Derived from the process of Intervention Mapping, two objectives for the VIP program were chosen: (1) office employees should be stimulated to increase their levels of daily physical activity by increasing active home-to-work transport and physical activity at work; (2) office employees should be stimulated to increase relaxation by increasing regular detachment during work hours. For developing the program, it was important to specify determinants for daily physical activity and relaxation. Based on the interviews, the most important determinants of daily physical activity and relaxation were: awareness, knowledge, attitude, subjective norm, self-efficacy and physical environment. Based on these determinants, methods and strategies were chosen. To specify the intervention program, tools and materials were selected to support the strategy. Decisions about suitable methods, strategies, tools and materials were made together with the project group and feedback from experts (Table 1). Subsequently, two components of the VIP program were chosen, i.e. (A) Group Motivational Interviewing (GMI), supported by a social media platform and (B) environmental modifications.

Table 1. Methods and Strategies of the VIP project

| **Determinant** | **Theoretical method** | **Practical strategy** | **Tools and materials** |
| --- | --- | --- | --- |
| *Awareness* | Self-monitoring | Monitoring of own behaviour | Dairy in workbook. Self complete logs to monitor own physical activity and relaxation behaviour in last week. |
| *Knowledge* | Passive learning/providing information | Provide written and verbal information | Promote current facilities of financial service provider on social media platform/intranet/ and give information during Group Motivational Interviewing sessions. |
| *Attitude* | Active processing of information/active learning | Brainstorming about barriers/Group discussion | A group discussion about barriers during Group Motivational Interviewing sessions. |
| *Subjective norm* | Mobilizing social support | Invite employees to formulate who can provide support | During a Group Motivational Interviewing session: discussion about who can provide support.  +  Employees can join or create physical activity and relaxation groups on the social media platform.  + Forum on social media platform with exchanging tips on daily physical activity/relaxation. |
| *Self efficacy* | Reinforcement  Goal setting | Provide positive feedback on changes in self efficacy: evaluation of changes  Facilitate formulation of goals | During Group Motivational Interviewing positive feedback will be given by teamleader and employees. Also new arguments to cope with difficult situations is given.  During Group Motivational Interviewing: Worksheets to help extract planning goals (when, where, with whom?). Discussion about barriers/ difficult situations and possible solutions. |
| *Physical environment* | Environmental changes | Change work environment | Ask for interior advice. Change colours/ lighting/ desks etc. |

(A) Group Motivational Interviewing (GMI)

Over the last years, the technique of individual Motivational Interviewing (MI) has gained strong empirical support in work settings (30-34). MI in work settings was implemented to improve health- related behaviours, such as physical activity, dietary behaviour, mental health, and to diminish substance abuse. There is increasing support that individual MI can be adjusted to a group format (35-40). Group motivational interviewing (GMI) uses the concepts of self-determination theory (41) and individual motivational interviewing (42). The essence of GMI is to apply the individual MI concepts to a group setting. A group setting has several benefits, i.e. sharing experiences, providing feedback and giving support (40). GMI helps to create an autonomous supportive environment, in which behaviour change is encouraged (36). Evidence for the beneficial effects of groups in work settings can be found in research on group education. For instance, an 8-week nutrition education group program developed for university employees, showed increased nutrition knowledge, reduced calorie intake and cholesterol intake (43). Another study of a 9-week group education program on diet and physical activity with university staff showed reduced lipid, glucose and insulin levels (44). Given that individual MI and group education programs have shown to be effective in work settings, it can be assumed that GMI in the work setting might be effective for lowering the need for recovery by improving daily physical activity and relaxation behaviour too. Supporting the GMI by a social media platform will help to improve effective communication, staying informed on news topics, finding answers and receiving help (45).

(B) Environmental modifications To date, most environmental modifications to improve a healthy lifestyle focused on healthy nutrition and improving physical activity (46). Examples are food labelling, changes in food offering, providing exercise space and exercise equipment, red line routes to promote lunch walking, posters to promote stair use and a walking track (46). Research has shown that changing work areas (i.e. office layout and/or office furniture) could positively influences employee's attitudes (47), job satisfaction and performance (48-51). For example, Vink et al. (52) asserted that redesigning the coffee corner, e.g. placing informal seats, will increase the number of conversations at the coffee corner. They found that these conversations were 4 out of 5 times about work and were beneficial to the employees’ productivity and creativity (52). Furthermore, in the study of Cohen et al. (53), it was demonstrated that the design of a meeting room, but also the lighting, noise and seating, may have impact on the quality of the meeting. Leach et al. (54) proved that environmental modifications to a meeting room will improve comfort for the employee and helps the employee to focus on the meeting. Other examples of effective interventions were placing stand-up tables, i.e. a previous study showed that stand-up meetings are faster than sit-down meetings (55); painting office walls, i.e. it has been discovered that this may positively influence productivity levels (56). Specifically, working in a red environment increases productivity, but it is more distracting than working in a white environment (57). A blue-green work environment is seen as more relaxing and is preferred by employees. On the negative side, a red colour reduces arousal levels and consequently productivity (57). Next, adjustment of lighting. That is, in the study of Veitch (48), employees worked under six different lighting conditions a day. When different lighting was applied, they were in a better mood and scored higher on well-being. Finally, modifications to decrease office noise (58). Concentration is reduced by telephone ringing and people talking in the background (59). Hearing problems during the day increases the need for recovery at the end of the day (60). Studies showed that sound-masking, placing indoor plants or indoor vegetation in the work environment are really appreciated (61) and increase a positive mood and performance (62).

# 2. Objectives and research questions: VIP in Insurance project

The primary objective of this study is to evaluate the effectiveness of the ‘VIP (Vitality in Practice) in Insurance’ program, i.e. GMI, supported by a social media platform, and/or environmental modifications, on the need for recovery, daily physical activity and relaxation levels in office employees. Secondary objectives are to evaluate the cost-effectiveness and cost-utility of the VIP program and to evaluate the process of implementation of the VIP program.

We hypothesize that the VIP program will significantly lower the need for recovery in office employees by increasing daily physical activity and relaxation, compared to the control group, both at short-term (6 months) and long-term (12 months) follow-up. We expect that the intervention arm with both the GMI-intervention and the environmental modifications will be more successful to lower the need for recovery in office employees, than the intervention arms with only GMI or only environmental modifications.

Research questions

The research questions of the ‘VIP in Insurance’ project are:

1) What are the effects of the VIP program on need for recovery in office workers?

2) What are the effects of the VIP program on daily physical activity and relaxation in office workers?

3) What are the cost-effectiveness and cost-utility of the VIP program from a societal and company perspective?

4) What are the strengths and weaknesses of the VIP program when implementing the program?

# 3. Methods

# 3.1 Population

The study sample consists of office employees (18-64 years) of a financial service provider in the Netherlands. The building of this financial service provider has 10 departments with 24 wings. Each wing has the capacity for 6 teams, corresponding with a total of 60-80 employees per wing. Wings on a department level are separated from one another. In the present study, teamleaders and their employees of 13 wings will be invited to participate. We decided to exclude 4 departments (11 wings) beforehand, since environmental modifications are already ongoing or planned in these departments.

#

# 3.2 Inclusion and exclusion criteria

Employees are eligible for participation in the study, when they are able to complete a Dutch (online) questionnaire and when they are expected to be employed at the financial service provider during the complete follow-up period. Employees will be excluded from the study, if they are on long-term sick leave (≥ 4 weeks) at baseline.

# 3.3 Design

In this study, a randomized controlled trial design will be employed, with pre-stratification on environmental modifications. That is, two strata will be created, with (6 wings) and without (7 wings) environmental modifications. Within each stratum, wings will be randomly assigned to GMI or no GMI. Randomisation will take place at wing level. We decided to apply cluster randomisation on wing level to avoid contamination with employees in the control group. Consequently, the study will consist of four research arms, i.e. (1) both GMI and the environmental modifications, (2) environmental modifications/no GMI, (3) GMI/no environmental modifications, (4) no GMI/no environmental modifications (control group). The design of the VIP project is shown in appendix 1.

# 3.4 Study procedures

Managers and directors of all potentially participating wings will be invited by email for a short VIP kick-off meeting. During this kick-off meeting, information about the VIP program will be given to the managers/directors and they will be asked to stimulate participation of their teamleaders and employees. Subsequently, all teamleaders (N=80) from 13 wings will be invited by email for an exclusive VIP kick-off meeting for teamleaders (approximately 45 minutes). During this meeting, information about the VIP program will be given and teamleaders will be asked to stimulate their employees to participate in the VIP program. Directly after this meeting, they will receive two envelopes: one with a letter and informed consent form, for themselves, and the other including all letters, informed consent forms and flyers for their employees. Employees have to give their consent for participation in the project and for obtaining data on sick leave. Data on sick leave and the duration of employment will be obtained from the HRM department, only when the employee has given his/her consent. After one week, the VIP researcher will personally collect all informed consent forms, both from the teamleader him/herself and his/her employees. In case of no response, a reminder will be sent to the teamleaders and the VIP researcher will visit them personally. Employees will be asked to give their email address on the informed consent form, which will be used for sending the online baseline questionnaire. It will be emphasized that they can only participate, when both the teamleader and more than half of the employees within a team have given their consent. Furthermore, a wing is only eligible for randomisation, when more than half of the teams within a wing have given their consent. When teamleaders and their employees are excluded from the VIP program, they will be informed by an email of the VIP researcher. A flow diagram of the VIP project is shown in appendix 2.

Randomisation of GMI will be performed after the baseline measurement (T0) and will be prepared and executed by an independent researcher, by using a computer generated list from SPSS. After baseline, extensive (online) questionnaire data will be gathered at 6 months (T1), and at 12 months (T2) follow-up, in both the intervention and the control group. At 3, 6, 9 and 12 months follow-up, data is gathered for the economic evaluation. At 6 and 12 months these questions will be added to the extensive online questionnaire. At 3 and 9 months these questions will be asked separately by a small online questionnaire. Furthermore, at 6 months follow-up (at the end of the intervention) questions to evaluate the program will be added. Reminders for the questionnaires will be sent, after one week. A timeline of the VIP project can be found in Appendix 3.

3.5 Sample size calculation The sample size calculation is based on the main outcome measure, i.e. need for recovery, measured by the need for recovery questionnaire (63). The mean need for recovery score is 27,30 (SD=29,75) according to the validation study of Van Veldhoven et al. (63). Minimal relevant difference on the need for recovery scale, with a range from 0 to 100, was set on 12. This was based on the articles by de Croon et al. (64) and Kuijer et al. (65), in which on average a relevant difference of 12 was found in nurses, truck drivers and refuse collectors, after an intervention, such as change in work hours (64) or job rotation (65). Using a power of 0.9, in total 260 employees are needed. Because randomisation takes place at wing level, a cluster correction was applied. An intraclass correlation (ICC) of about 0.025 is assumed, based on previous studies showing that worksite level ICC’s for health-related outcomes are generally small (66-68). This leads to a cluster correction factor of 1 + (13-1)* 0.025 = 1.3. Based on this cluster correction, a total of 1.3*260 = 338 employees will be needed. Furthermore, by applying a correction for repeated measurement we will win some precision, therefore an additional correction by a factor 0.9 seems justified, resulting in 0.9×338=305 employees in total. Finally, accounting for a loss to follow-up of 25% in twelve months, a total of 404 employees for the four intervention arms will be needed at baseline. Based on the source population of 980 employees (13 wings), the number of 404 employees is reached at a participation rate of 42 percent. This percentage is considered feasible, because all teamleaders and their employees within a wing will be asked to participate.

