# 4.4.2 (B). Environmental modifications

Environmental modifications will be applied to two departments (six wings). The environmental modifications will focus on facilitating daily physical activity and relaxation in the work environment, by changing the coffee corners, the open office environment, the meeting rooms and the entrance hall. Coffee corners will be adapted by adding bar chairs, magazines on the tables, an electronic dartboard, indoor plants, relaxing lights and by painting the coffee corner walls. In addition, the open office environment will be changed by introducing exercise balls, standing desks, sound masking to reduce background noise, and indoor plants. The interior of the meeting rooms will be changed by placing a stand-up table, a lamp, an indoor plant and by painting the walls. Furthermore, a ping-pong table and an indoor plant will be placed in the entrance hall. Prompts of decisions posters to promote daily physical activity and relaxation will be attached on the walls of the coffee corner and the entrance hall. In addition, food steps will be placed on the floor by the entrance hall to promote stair walking. All these environmental modifications will be promoted by posters in the coffee corner and in the hallway. Furthermore, the employees and the teamleaders will receive information by email about the environmental modifications.

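### Wing allocation is drawn after baseline but uses none of the wing-level baseline data; drawing from a balanced set of allocations would be a cheap improvement on a valid design

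*Protocol*

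**What the plan says.** Section 3.3 sets the unit and the restriction: "Randomisation will take place at wing level", "two strata will be created, with (6 wings) and without (7 wings) environmental modifications", and "Within each stratum, wings will be randomly assigned to GMI or no GMI". Section 3.4 sets the timing, "Randomisation of GMI will be performed after the baseline measurement (T0"), and the mechanism, "prepared and executed by an independent researcher, by using a computer generated list from SPSS". Appendix 1 fixes the counts: 3 GMI and 3 non-GMI wings with modifications, 4 GMI and 3 non-GMI wings without. No matching, minimisation or balance criterion on wing characteristics is described.

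Section 4.4.2 adds that "Environmental modifications will be applied to two departments (six wings"). Section 6 plans a multilevel model with correction for baseline values, crude and confounder-adjusted analyses (gender and age are the named examples), and an effect estimate in each stratum as well as a pooled one.

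**The concern.** Few units are randomised, so chance differences between the GMI and no-GMI wings can be sizeable, above all within a stratum, where an effect is also to be estimated. The protocol is well placed to limit this: T0 is complete, the list is drawn by someone independent, and each wing's mean need for recovery, number of participants and department are known. It uses none of these.

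Some imbalance can be corrected in the analysis and some cannot. Individual baseline need for recovery, age and gender can go in the model. Department and wing size are not named as adjustment variables, and three wings against three, or four against three, leave little room to add them. If all GMI wings in the modified stratum fell in one of its two departments, and the non-GMI wings in the other, no model could separate GMI from department there. Allocation belongs in the protocol and cannot be repaired once drawn.

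**Working it through.** **Inputs.** SD 29.75 (section 3.5: "The mean need for recovery score is 27,30 (SD=29,75")), target difference 12, ICC 0.025, and 404 employees ("a total of 404 employees for the four intervention arms will be needed at baseline"), all from section 3.5. Wings: 3/3 and 4/3 (Appendix 1). Wing size: 404/13 = about 31.

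**The plan's own figure.** The protocol gives no figure for imbalance. Its starting sample size does reproduce: 2 × (1.960 + 1.282)² × 29.75² / 12² = 129.2, so 130 per group and 260 in total, as stated. The SD and the target are therefore read as the protocol uses them.

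**Size of the chance baseline difference.**
- Variance of a wing mean: 29.75² × (0.025 + 0.975/31) = 49.96, SD 7.07.
- Six-wing stratum (3 v 3): 7.07 × √(1/3 + 1/3) = 5.77 points.
- Seven-wing stratum (4 v 3): 7.07 × √(1/4 + 1/3) = 5.40 points.
- Pooled by inverse variance: √[1/(1/5.77² + 1/5.40²)] = 3.94 points.

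**Chance of a difference above 6 points** (half the target; the threshold is my choice), taking wing means as Normal:
- Six-wing stratum: 6/5.77 = 1.04, so 30%.
- Seven-wing stratum: 6/5.40 = 1.11, so 27%.
- At least one stratum: 1 − (0.70 × 0.73) = about 49%.
- Pooled: 6/3.94 = 1.52, so 13%. For 12 points, 12/3.94 = 3.04, so 0.2%.

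**Sensitivity to the ICC** (same formulas):

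| ICC | Pooled above 6 | At least one stratum above 6 |
|---|---|---|
| 0 | 4% | 29% |
| 0.01 | 8% | 38% |
| 0.025 | 13% | 49% |
| 0.05 | 20% | 60% |
| 0.10 | 31% | 73% |

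Using Appendix 1's 202 per stratum instead (about 34 and 29 per wing) changes little: simulation gives SDs of 5.6, 5.5 and 3.9, with 12% pooled.

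**Department.** The split of the six modified wings over the two departments is not given. If it is 3 and 3, then 2 of the C(6,3) = 20 draws (10%) put all three GMI wings in one department and all three non-GMI wings in the other. If it is 4 and 2, C(4,3)/20 = 20% put all GMI wings in the larger department, where GMI and department are then only partly aligned.

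**What balancing achieves.** There are C(6,3) × C(7,4) = 20 × 35 = 700 allocations. With a 3 and 3 split, excluding one-department draws leaves 18 × 35 = 630. I simulated baselines at ICC 0.025 and 31 per wing, and scored allocations by the sum of squared stratum differences in wing mean need for recovery and in wing size (equal weights, independent variables). Drawing from the best 140 gives an SD of about 2.2 points pooled and about 3.3 in the six-wing stratum. Balancing need for recovery alone would give about 1.5 and 2.2, but that is not the proposal. On a Normal approximation, the six-wing chance of exceeding 6 points falls from 30% to about 7% (6/3.3 = 1.82).

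**The case against.** The strongest reply is that nothing here is wrong. Stratified cluster randomisation by an independent person is valid and unbiased, and the absence of a balance criterion is inferred from silence. That stands: this is a missed improvement, not an error or a contradiction.

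A reader might go further and infer that a large imbalance is likely. The documents do not support that. On the protocol's own figures a pooled difference above 6 points has about a 13% chance, and one of 12 points about 0.2%. Near-even odds appear only when counting at least one of the two strata.

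The figures above are also raw baseline differences, not errors in the planned estimate. Section 6 corrects for baseline values and for confounders. At ICC 0.025 and 31 per wing, 0.025/(0.025 + 0.975/31) = 44% of the variance of a wing mean is true between-wing variance. The rest is individual sampling variation, the kind that individual baseline adjustment addresses. The true-wing part of the pooled SD is 3.94 × √0.44 = 2.6 points before any adjustment. This stands too, and limits the gain for the primary outcome.

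Finally, putting every balancing variable in the model would defeat the purpose. Sections 3.1 and 4.4.2 imply two modified departments and four unmodified ones. Intercept, GMI, department, wing size and wing mean need for recovery then take 5 wing-level parameters for 6 wings in one stratum, and 7 for 7 in the other. That is why department is handled below by exclusion, not by fixed effects.

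What the reply does not answer is department and wing size, which the planned adjustment does not name. Nor can balancing do everything: three GMI wings over two three-wing departments split 2:1 at best, and management and workload remain to chance.

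**Conclusion.** The point holds as a cheap improvement to a valid design. The chance baseline difference has an SD of 3.9 points pooled and 5.8 in the six-wing stratum, and exceeds 6 points in about 13% of draws pooled and about 49% in at least one stratum. Much of this is absorbed by the planned correction for the primary outcome. What remains is exposure to department and wing-size imbalance, mainly in the stratum estimates, including a 10% chance of complete alignment of GMI with department in the modified stratum if its departments have three wings each.

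The figures rest on the protocol's SD and ICC, equal wing sizes, Normal wing means, the 6-point threshold and, for the 10%, the assumed 3 and 3 split. I have not put a figure on the error left after the planned model.

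**What to change.** Add a paragraph to section 3.4. Keep the two strata and the 3/3 and 4/3 counts. After T0 the independent researcher:

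1. lists all 700 allocations;
2. excludes those that put all GMI wings of the modified stratum in one department;
3. scores the rest on balance in wing mean baseline need for recovery and wing size, by a formula fixed beforehand;
4. draws one at random from an acceptable set of pre-set size, for example 140.

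State the size of the set also as a proportion, since section 3.4 lets a wing drop out before randomisation if too few teams consent. If the departments split 4 and 2, apply the exclusion to the non-GMI wings as well. If they split 5 and 1, drop it, because it would fix the single wing's allocation.

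In section 6, include wing size in the multilevel model beside baseline need for recovery, which is already planned. Do not add department as fixed effects; 6 or 7 wings per stratum cannot carry them.

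The cost is a short script and a few sentences, with no extra participants, measurements or delay. The downsides are one more wing-level covariate and the need to keep the acceptable set wide enough that the draw stays properly random.
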